#### Magnetic resonance imaging (MRI)

Whole-body MRI, including conventional MRI (T1 weighted and STIR sequences) and an MRI sequence used for synthetic CT reconstruction (3D gradient echo sequences), will be performed on all patients at baseline, month 4, month 12, and month 24.

WB-MRI will be performed with patients in a supine position and for the following areas: 1. coronal images of shoulders and anterior chest wall; 2. sagittal images of the cervical, thoracic, and lumbar spine; 3. coronal images of the pelvis and hips; 4. coronal images of hands (positioned under the buttocks); 5. sagittal images of knees; 6. sagittal images of ankles; and 7. axial images of the ankles/feet. 3 mm slice thickness (ST) will be used for hand, wrist, and forefeet (in-plane resolution 0.6x0.6 mm), 4 mm ST for spine and SIJ, and 5 mm ST for anterior chest wall, shoulders, pelvis, knee, and ankles (in-plane resolution 0.5x0.5 mm).

The MRI scans will be performed on a 3 Tesla MRI unit.

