### Participants

Participants will be recruited from rheumatological outpatient clinics in the capital region of Copenhagen. Participants in this study are all patients followed by the participating rheumatologic departments. The participant must have moderate to high disease activity, and it must have been decided by the individual departments (at a conference between rheumatologists), that the patient should start or switch biologic treatment.

The patient is invited to participate in the study by a physician in the rheumatological outpatient clinic during a routine visit. Oral and written information will be provided. If the patient agrees to participate, an informed consent form is signed. A screening visit is performed to ensure that the patient meets the criteria for participation.

Inclusion criteria for both groups (axSpA and PsA) are age $$ \ge $$ 18 years at the time of consent, a clinical indication for a biological drug as assessed by the treating physician, sufficient contraception for women in addition to the ability and willingness to provide written informed consent and compliance with the requirements of the study protocol.

For patients with axSpA additional inclusion criteria are a diagnosis of axSpA according to the Assessment of SpondyloArthritis International Society (ASAS) classification criteria [27, 28], active inflammation on MRI of the SIJs and/or spine [29] as evaluated by a central SpA imaging expert and/or radiographic modified New York criteria [30] fulfilled, and total back pain as measured on a VAS scale ≥40 mm (0–100 mm) at baseline.

For patients with PsA additional inclusion criteria are PsA according to Classification Criteria for Psoriatic Arthritis (CASPAR) [31], negative rheumatoid factor (RF) and anti-cyclic citrullinated peptide (anti-CCP), and ≥ 1 tender and swollen joint in addition to two further anatomical localizations with clinical signs of inflammation (i.e., tender enthesis and/or tender and/or swollen joint) assessed at screening and baseline. For patients to fulfill the axial PsA component they must have imaging documented axial involvement on MRI, radiography, or low-dose CT as judged by a central SpA imaging expert.

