#### Other assessments

Details of other assessments (clinical, composite, and patient-reported assessments) are provided in Table 1 and a summary of all measures to be collected is provided in Table 2.

**Table 1 Tab1:** Details of clinical, composite and patient-reported assessments

Clinical evaluation and composite indices	
Inflammatory back pain (ASAS definition)	Criteria set for inflammatory back pain according to ASAS experts include age at onset < 40 years, insidious onset, improvement with exercise, no improvement with rest, and pain at night [35].
ASDAS CRP	A composite measure of disease activity based on CRP, VAS of patient global assessment of disease activity (0–100 mm), back pain (0–100 mm), duration of morning stiffness (0–100 mm), and peripheral pain/swelling (0–100 mm) [36].
BASMI	Five measurements of different movements are performed, including intermalleolar distance, flexion and lateral flexion of the lumbar spine, tragus-wall distance, and rotation of the neck [37].
DAS28 CRP	An index based on tender and swollen joint count of 28 peripheral joints, patient global assessment of disease activity, and CRP [38].
CDAI	CDAI is a composite index based on tender and swollen joint count and patient and physician global assessment of disease activity on VAS [39].
Swollen and tender joint count	In total 66 joints are examined for swelling and 68 for tenderness in all patients. The following joints are examined: right and left temporomandibular joint, sternoclavicular joint, acromioclavicular joint, glenohumeral articulation, elbow joint, wrist, 10 MCP joints, 10 PIP- and DIP joints in the hands and 10 toes and MTP-joints, tarsus/midfoot joint, ankle joint, knee joint, hip joint (for tenderness only).
SPARCC Enthesitis Index	SPARCC Enthesitis index comprises 18 anatomical sites, nine on the right side and nine on the left side: Insertion of supraspinatus, lateral and medial epicondyle humerus, greater trochanter, quadriceps insertion into the superior border of patella, patellar tendon insertion into the inferior pole of patella or tibial tubercle, Achilles tendon and insertion plantar fascia, with a score of 0–16 (for scoring purpose, the inferior patella and tibial tuberosity are considered one site because of their anatomical proximity) [40].

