Leeds Enthesitis Index	LEI comprises six anatomical sites: The lateral epicondyle of humerus (left/right), the medial epicondyle of femur (left/right), and the Achilles tendon (left/right), with a score of 0–6 [41].
DAPSA	An index based on swollen and tender joint counts, patient global and pain assessment, and CRP [42]
Minimal Disease Activity (MDA)	A state of MDA for PsA has been established and is defined by a low activity of disease assessed by tender/swollen joint counts, tender entheseal points, Psoriasis Area and Severity Index or body surface area, patient pain and global activity VAS, and functional evaluation by Health Assessment Questionnaire (HAQ) [42].
Physician global assessment	The physician evaluates the overall disease activity of the patient (VAS 0–100 mm).
Extraarticular SpA features	Evaluation of presence of symptoms/signs of activity in the following extraarticular SpA features: anterior uveitis or scleritis, inflammatory bowel disease, dactylitis, skin or nail psoriasis, and heel enthesitis.
Tender points	Tender points are defined by the ACR as 18 points on the body, nine on one side, and nine on the other, where pain can be felt immediately beneath the skin when pressed. According to the 1990 ACR guidelines, fibromyalgia could be diagnosed based on the presence of tender points [43].
BSA	BSA assessment measures the total area of the body affected by psoriasis. Psoriasis that occurs in less than 5% of the BSA is considered mild, 5–10% is moderate and if psoriasis affects more than 10% of the BSA, it is severe. Hand surface area (HSA) or palm surface area (PSA) is commonly used for the estimate, with an assumption that HAS represents 1% and PSA (approximately equal to the palm of the patient’s hand, excluding fingers) represents 0,5% of BSA in adults [44].
Nail involvement, absence/presence of psoriasis	Nail involvement will be evaluated for psoriatic changes such as onycholysis, pitting, and hyperkeratosis with a count of the number and location of affected nails (presence/absence of psoriatic change) [42].

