### Endpoints

#### Primary endpoint

The primary endpoint is the change from baseline to month 12 in the total inflammatory burden in the entire body (peripheral and axial joints and entheses), as assessed by WB-MRI, in patients with axSpA and PsA treated with ixekizumab.

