**Other secondary endpoints**	
1.	Change from baseline to *months 4, 12, and 24* in *axial inflammation*, as assessed by MRI, in patients with axSpA and PsA treated with ixekizumab, including separately in the posterolateral elements of the spine (facet joints, costovertebral joints, transverse processes, spinous processes, and perientheseal soft tissues) and in the vertebral bodies.
2.	Change from baseline to *months 4 and 24* in *peripheral enthesitis*, as assessed by WB-MRI, in patients with axSpA and PsA treated with ixekizumab.
3.	Change from baseline to *months 4 and 24* in *peripheral joint inflammation*, as assessed by WB-MRI, in patients with axSpA and PsA treated with ixekizumab.
4.	Change from baseline to *month 4* in *total inflammatory burden in the entire body* (peripheral and axial joints and entheses), as assessed by WB-MRI, in patients with axSpA and PsA treated with ixekizumab.
5.	*Description of differences between axSpA and PsA* inflammatory disease manifestations and their response to ixekizumab therapy at months 4, 12, and 24 (by sacroiliac joint and spine MRI and by WB-MRI).
6.	*Development of improved MRI and CT assessment methods* for axial structural damage assessment.
7.	Description of the *relationship between clinical, patient-reported, and imaging findings* at baseline and during ixekizumab therapy.

*WB-MRI* Whole body magnetic resonance imaging, *axSpA* axial spondyloarthritis, *PsA* Psoriatic arthritis, *CT* computed tomography

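### The listed WB-MRI areas leave out the elbows, which carry 25% of SPARCC and 33% of Leeds enthesitis points: the endpoint label overstates coverage and the clinical-imaging comparison of enthesitis needs matched sites

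*Protocol article*

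**What the plan says.** **Imaged field.** The MRI section of the protocol article numbers seven areas: shoulders with anterior chest wall, whole spine, pelvis with hips, then "coronal images of hands (positioned under the buttocks); 5. sagittal images of knees; 6. sagittal images of ankles", and finally the ankles/feet. A second list gives slice thickness by region, for example "5 mm ST for anterior chest wall, shoulders, pelvis, knee, and ankles". Neither list contains the elbow or the temporomandibular joint, and nothing says that another field covers them.

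**Clinical indices.** Table 1 (Other assessments) includes the temporomandibular joint in the 66/68 joint count, and also "glenohumeral articulation, elbow joint, wrist, 10 MCP joints". The SPARCC Enthesitis Index starts with "Insertion of supraspinatus, lateral and medial epicondyle humerus". For the Leeds index, "LEI comprises six anatomical sites: The lateral epicondyle of humerus (left/right") opens the list.

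**PsA entry.** The Participants section asks for at least one tender and swollen joint plus "two further anatomical localizations with clinical signs of inflammation (i.e., tender enthesis and/or tender and/or swollen joint"). No site is named or excluded.

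**Endpoints.** The primary endpoint is the month 12 change in "the total inflammatory burden in the entire body (peripheral and axial joints and entheses"). The Statistical analysis section computes this total, and WB-MRI remission, from the sum of WIPE, CANDEN spine and SPARCC SIJ. Other secondary endpoint 7 (Table 3) describes the "relationship between clinical, patient-reported, and imaging findings", and the Statistical analysis section plans correlation analyses between imaging and clinical findings.

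**The concern.** The Introduction and Discussion argue that clinical assessment of enthesitis is uncertain and that WB-MRI gives an objective view of joints and entheses over the whole body. That argument needs the two methods to look at the same places. If a clinical index counts sites that the scan does not reach, part of any disagreement reflects coverage. A reader could take it for clinical error, which is the direction the study's rationale already favours.

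The label has a similar problem. Active elbow disease cannot raise the MRI total, cannot show improvement in key secondary endpoints 1 and 2, and cannot count against WB-MRI remission. A PsA patient may meet the entry rule partly or wholly through such sites.

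**Working it through.** **1. Share of each index outside the listed field** (sites as itemised in Table 1)

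- SPARCC: lateral and medial humeral epicondyle, both sides = 4 of 16 points = 25%. The other 12 points (supraspinatus, greater trochanter, quadriceps, patellar tendon, Achilles, plantar fascia, two sides each) lie in listed areas.
- Leeds: lateral humeral epicondyle, both sides = 2 of 6 points = 33%. The other 4 (medial femoral epicondyle, Achilles) lie in listed areas.
- Joint counts: 2 elbows + 2 temporomandibular joints = 4/66 = 6.1% for swelling and 4/68 = 5.9% for tenderness. Elbows alone are 2/66 = 3.0% and 2/68 = 2.9%.
- The joints in DAS28 and CDAI are not itemised. DAPSA and MDA are described only as using joint or entheseal counts. No share can be computed for these.

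**2. How far missing coverage alone could lower a correlation**

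Suppose MRI agreed perfectly with the clinical finding at every imaged site. The correlation with the full index would then equal that between the sum over the k imaged sites and the sum over all m sites. With equal variances and a common inter-site correlation ρ (both assumed, since the documents give neither):

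corr = k[1+(m−1)ρ] / √{ k[1+(k−1)ρ] × m[1+(m−1)ρ] }

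| ρ | Leeds (k=4, m=6) | SPARCC (k=12, m=16) |
|---|---|---|
| 0 | √(4/6) = 0.82 | √(12/16) = 0.87 |
| 0.3 | 10/√(7.6×15) = 0.94 | 66/√(51.6×88) = 0.98 |
| 0.5 | 14/√(10×21) = 0.97 | 102/√(78×136) = 0.99 |

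The built-in loss is clear if sites are independent and small if they are moderately correlated.

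**3. Does the gap endanger the primary test?**

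The plan's own figures first. The SD is 3.6×√53 = 26.2, as stated. For a paired t-test with mean change 24.8, SD 26.2 and two-sided 0.05, noncentral-t power is 0.807 with 11 pairs and 0.847 with 12, so the stated 12 pairs suffice.

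Next, let the missing elbows reduce the mean change with the SD unchanged. The size of the reduction is an assumption. The documents do not say which joints the earlier golimumab study imaged, so it may be zero.

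| Reduction in mean change | 20 completers (25 less 20%) | 52 completers (65 less 20%) |
|---|---|---|
| none | 0.98 | >0.99 |
| 5% | 0.97 | >0.99 |
| 30% | 0.80 | 0.997 |
| 50% | 0.52 | 0.92 |

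The overall test holds throughout. A 25-patient diagnosis group holds up to about a 30% reduction, and nothing in the documents suggests a loss that large.

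**The case against.** The strongest reply is that the endpoint has an operational definition. It is a sum of scores that the article calls validated, and the whole-body phrase is only its name. The same areas are scanned at every visit, so an omitted site narrows the measurement without biasing within-patient change. That stands. A reader might infer that the primary analysis is invalid or underpowered; the documents do not support this. Nor can one tell whether the scan departs from WIPE, since the article does not list the sites WIPE scores.

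Secondly, the article nowhere commits to correlating whole Leeds or SPARCC totals with MRI scores. Endpoint 7 is worded generally, and a detailed SAP is promised before any analysis. This also stands: the mismatch is a risk to be closed in that SAP and is not an error already made.

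Thirdly, a reader might infer that every clinical index is affected. Only the 66/68 count, SPARCC and Leeds can be shown to be, and the joint count barely.

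Fourthly, entry through elbow sites alone is possible on the wording, for example with both elbows and an epicondyle. No frequency is given, however, and the text does not say whether adjacent sites count as separate localizations. It should not be assumed to be common.

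What survives is narrower: an unscanned elbow cannot be read, whatever WIPE scores, and a quarter to a third of the enthesitis points lie there.

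**Conclusion.** The concern holds for enthesitis and for wording. On the areas listed, 25% of SPARCC points and 33% of Leeds points have no imaging counterpart. If full indices are compared with WB-MRI, coverage alone would limit the correlation to somewhere between 0.82 and about 0.94 for Leeds and between 0.87 and about 0.98 for SPARCC, for inter-site correlations from 0 to 0.3. These limits are illustrations that rest on equal site variances and perfect agreement at imaged sites. The effect on joint counts is minor. The primary within-patient comparison is sound on this point; what needs limiting is the claim attached to it and to WB-MRI remission, since both describe the imaged regions only.

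**What to change.** - **Endpoint 7.** In the SAP, prespecify a site-matched clinical-imaging comparison for enthesitis, using imaged sites only (Leeds 0-4, SPARCC 0-12), reported together with the full published indices.
- **Wording.** Describe the MRI total and WB-MRI remission as inflammation in the imaged regions, and state that the elbows and temporomandibular joints are not among the listed areas.
- **Entry.** Report descriptively how many PsA patients met the entry criterion only through sites that are not imaged.

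This changes analysis and text only; no scan, visit or eligibility rule is altered. It depends on joints and entheses being recorded site by site in the case report form, which the article does not state and which should be confirmed first. The downside is that the restricted scores are not the validated totals, which is why both are shown.

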#### MRI-based synthetic CT

BoneMRI or “synthetic CT” is a quantitative 3D MRI technique, developed by the company MRIGuidance BV, NL, based on a multiple gradient-echo sequence (TR, TE, FlipAngle of 7 ms, 2 ms, and 3.5 ms and 10°; ST 0.8 and in-plane resolution 0.6x0.6 mm) and a machine learning processing pipeline [32]. The BoneMRI technology can generate CT-like, quantitative radiodensity bone MRI images to visualize cortical and trabecular bone, allowing assessment of bone structure and morphology.

The bone MRI sequences will be reconstructed by MRIGuidance BV, NL, using the BoneMRI model. MRIGuidance BV, NL will have no access to other MR images, CT images, or radiographs during the study.

#### Computed tomography

Low-dose CT of the spine (cervical, thoracic, and lumbar spine) and SIJs will be performed at baseline and repeated at months 12 and 24.

The low-dose CT is performed in a photon-counting CT scanner using a dedicated low-dose protocol. The kilovoltage peak is set at Sn100 kVp, and automated tube current modulation is used. The scan field of view is 50 cm. Quantum iteration level 3 is used, the pitch is 0.5, collimation 144 × 0.4, and rotation time 0.5 s. The requested CT-dose index is 1.36 mGy. The total examination time is approximately 10 minutes. The axial images are reconstructed in sagittal and coronal planes for the spine and coronal- and axial-oblique planes for the SIJs.

#### Radiography

Radiographs of the SIJs and spine (cervical and lumbar spine) will be performed at baseline and repeated at month 24. The projections will be performed with the patient in a standing position in accordance with the mSASSS recommendations [33], and include anterior-posterior pelvis, and lateral cervical and lumbar spine projections. The total examination time is approximately 15 minutes.

#### Image evaluation

Image evaluation will be by state-of-the-art internationally validated methods for radiographs (modified New York criteria [30] and the mSASSS [33] method), MRI (SPARCC sacroiliac inflammation [17] and structural (SSS) [34] scores, Canada-Denmark spine score of inflammation and damage [19, 20]), and OMERACT Whole-body MRI scores of peripheral enthesitis and joint inflammation scores (WIPE) [13, 14]. Images will be evaluated by readers blinded for diagnosis and clinical and other imaging findings. Furthermore, new lesion definitions and evaluation methods for synthetic CT and low-dose CT will be sought developed and explored.

#### Other assessments

Details of other assessments (clinical, composite, and patient-reported assessments) are provided in Table 1 and a summary of all measures to be collected is provided in Table 2.

**Table 1 Tab1:** Details of clinical, composite and patient-reported assessments

Clinical evaluation and composite indices	
Inflammatory back pain (ASAS definition)	Criteria set for inflammatory back pain according to ASAS experts include age at onset < 40 years, insidious onset, improvement with exercise, no improvement with rest, and pain at night [35].
ASDAS CRP	A composite measure of disease activity based on CRP, VAS of patient global assessment of disease activity (0–100 mm), back pain (0–100 mm), duration of morning stiffness (0–100 mm), and peripheral pain/swelling (0–100 mm) [36].
BASMI	Five measurements of different movements are performed, including intermalleolar distance, flexion and lateral flexion of the lumbar spine, tragus-wall distance, and rotation of the neck [37].
DAS28 CRP	An index based on tender and swollen joint count of 28 peripheral joints, patient global assessment of disease activity, and CRP [38].
CDAI	CDAI is a composite index based on tender and swollen joint count and patient and physician global assessment of disease activity on VAS [39].
Swollen and tender joint count	In total 66 joints are examined for swelling and 68 for tenderness in all patients. The following joints are examined: right and left temporomandibular joint, sternoclavicular joint, acromioclavicular joint, glenohumeral articulation, elbow joint, wrist, 10 MCP joints, 10 PIP- and DIP joints in the hands and 10 toes and MTP-joints, tarsus/midfoot joint, ankle joint, knee joint, hip joint (for tenderness only).
SPARCC Enthesitis Index	SPARCC Enthesitis index comprises 18 anatomical sites, nine on the right side and nine on the left side: Insertion of supraspinatus, lateral and medial epicondyle humerus, greater trochanter, quadriceps insertion into the superior border of patella, patellar tendon insertion into the inferior pole of patella or tibial tubercle, Achilles tendon and insertion plantar fascia, with a score of 0–16 (for scoring purpose, the inferior patella and tibial tuberosity are considered one site because of their anatomical proximity) [40].
Leeds Enthesitis Index	LEI comprises six anatomical sites: The lateral epicondyle of humerus (left/right), the medial epicondyle of femur (left/right), and the Achilles tendon (left/right), with a score of 0–6 [41].
DAPSA	An index based on swollen and tender joint counts, patient global and pain assessment, and CRP [42]
Minimal Disease Activity (MDA)	A state of MDA for PsA has been established and is defined by a low activity of disease assessed by tender/swollen joint counts, tender entheseal points, Psoriasis Area and Severity Index or body surface area, patient pain and global activity VAS, and functional evaluation by Health Assessment Questionnaire (HAQ) [42].
Physician global assessment	The physician evaluates the overall disease activity of the patient (VAS 0–100 mm).
Extraarticular SpA features	Evaluation of presence of symptoms/signs of activity in the following extraarticular SpA features: anterior uveitis or scleritis, inflammatory bowel disease, dactylitis, skin or nail psoriasis, and heel enthesitis.
Tender points	Tender points are defined by the ACR as 18 points on the body, nine on one side, and nine on the other, where pain can be felt immediately beneath the skin when pressed. According to the 1990 ACR guidelines, fibromyalgia could be diagnosed based on the presence of tender points [43].
BSA	BSA assessment measures the total area of the body affected by psoriasis. Psoriasis that occurs in less than 5% of the BSA is considered mild, 5–10% is moderate and if psoriasis affects more than 10% of the BSA, it is severe. Hand surface area (HSA) or palm surface area (PSA) is commonly used for the estimate, with an assumption that HAS represents 1% and PSA (approximately equal to the palm of the patient’s hand, excluding fingers) represents 0,5% of BSA in adults [44].
Nail involvement, absence/presence of psoriasis	Nail involvement will be evaluated for psoriatic changes such as onycholysis, pitting, and hyperkeratosis with a count of the number and location of affected nails (presence/absence of psoriatic change) [42].
